#### Investigating the clinical implications of using iFOBT in general practice

Age- and sex-standardised number and rates of colonoscopies and urgent referrals in the CPP are estimated before and after intervention. Findings by colonoscopy are identified by ICD-10 codes, and the PPV of finding serious bowel disease is calculated. Serious bowel disease is defined as: CRC, inflammatory bowel disease or adenomas >1 cm. The number of CRCs diagnosed in the study period is compared with the number of CRCs diagnosed before introducing iFOBT in general practice. The same comparison is done for stage distribution of CRC.

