### Outcomes

The uptake and clinical use of iFOBT in general practiceFrequency of each indication used for requesting iFOBT○ Indications are registered when the GP orders the test. It is possible to tick the indications from the clinical instruction, and a box for other symptoms.Rate and frequency of iFOBT use and characteristics of the patients included.The GPs’ action on a positive test result (≥50 μg/L)○ According to the clinical instruction, a positive iFOBT result should imply referral to colonoscopy.The GPs’ action on a negative test result (≤49 μg/L)○ This outcome will evaluate how patients with a negative test result are followed up.

The diagnostic value of using iFOBT in general practiceAge- and sex-standardised number and rates of positive tests (>50 μg/L)Overall positive predictive value (PPV) for having CRC when iFOBT is positivePPV of having CRC in relation to iFOBT cut-off

The clinical implications of using iFOBT in general practiceAge- and sex-standardised number and rates of urgent referral in the CPP for CRCAge- and sex-standardised number and rates of colonoscopiesAll findings of colonoscopy on patients with a positive iFOBT (all ICD-10 codes determined at colonoscopy)Age- and sex-standardised number of CRCs diagnosedStage distribution of all CRCs diagnosed (I–IV)

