### Data collection

All citizens in Denmark are registered in the Danish Civil Registration System with a unique personal identification number (CPR number). This identification number is used in all national registers and enables accurate linkage between national registers [52]. Statistics Denmark will provide data on socioeconomic and demographic factors [53]. Data on iFOBT value and indications for use of iFOBT will be provided by the Department of Clinical Biochemistry at Randers Regional Hospital through the clinical laboratory information system research database [54]. Data on colonoscopy and comorbidity are extracted from the Danish National Patient Register [55]. Data on CRC diagnosis and disease stage are extracted from the Danish Colorectal Cancer Database.

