### Sample size

Each included GP is estimated to request 1–2 iFOBTs per week. This estimate is based on a previous report investigating Danish citizens’ reasons for encounter with a GP [56]. When taking into account that the study is rolled out sequentially and the study period is 1 year, we expect that 33,600 iFOBTs will be performed during the study period. Unpublished data from the Danish screening programme reveal that 6–10 % of performed iFOBTs are positive (≥100 μg/L) depending on age and gender. As this study uses a lower cut-off value (50 μg/L) and the investigated population is symptomatic, we estimate that approx. 10 % of performed tests will be positive. Screening studies have shown that the PPV of having CRC when the iFOBT is positive is approx. 10 % [26, 28, 29]. Therefore, we estimate that 10 % of the patients with a positive test will be diagnosed with CRC. In total, we expect to find approx. 336 CRCs by the use of iFOBT during the study period. Approx. 800 CRCs are annually diagnosed in the CDR. Using an alfa of 0.05 and a power of 0.8, we will be able to show a significant reduction in stage IV cancers from 25 to 16 % of annual CRC. However, as a reduction of this scale is unlikely, the study may be underpowered for this secondary outcome.

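### The serious bowel disease PPV needs adenoma size, but colonoscopy findings are to be identified by ICD-10 codes, and no named source is said to supply size

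*Protocol article*

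**What the plan says.** Under Statistical analysis, in the part on clinical implications, the protocol article gives the method: "Findings by colonoscopy are identified by ICD-10 codes, and the PPV of finding serious bowel disease is calculated". The next sentence gives the target condition: "Serious bowel disease is defined as: CRC, inflammatory bowel disease or adenomas >1 cm".

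The Outcomes section uses the same basis. It lists the colonoscopy findings of patients with a positive iFOBT and explains them in brackets as "all ICD-10 codes determined at colonoscopy".

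Data collection names the sources. For colonoscopy it says "Data on colonoscopy and comorbidity are extracted from the Danish National Patient Register". For cancer it says "Data on CRC diagnosis and disease stage are extracted from the Danish Colorectal Cancer Database". The other sources are the civil register for linkage, Statistics Denmark for socioeconomic and demographic factors, and the laboratory database for the iFOBT value and indication.

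**The concern.** The definition and the method do not fit. To decide whether a patient with an adenoma has serious bowel disease, the analyst needs the lesion's diameter. The method supplies a diagnosis code, which says what kind of lesion it is and where, but not how large it is.

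An analyst who follows the text therefore has to choose between counting every coded adenoma and counting none. Neither matches the published definition, and the choice would be open until the data are in hand. The result bears on the third aim, the clinical implications of case finding. The article's own discussion of the cut-off weighs false positives and colonoscopy resources, and the yield of serious disease among positives informs that balance.

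**Working it through.** The article states no figure for this PPV, so there is none to reproduce. The check compares the attribute each component needs with what the named sources are said to give, and then illustrates the effect.

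**Components against sources**
- CRC: needs a diagnosis. Available from codes and from the cancer database.
- IBD: needs a diagnosis. Available from codes.
- Adenoma above 1 cm: needs a diagnosis and a diameter. Codes give the first only. No named source is said to give the second, and no proxy for the threshold is stated.

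That ICD-10 classifies benign colorectal neoplasms by type and site and not by size is general knowledge of the classification; the article does not say it.

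**Inputs from the article (Sample size)**
- Tests: "we expect that 33,600 iFOBTs will be performed during the study period".
- Positivity: "we estimate that approx. 10 % of performed tests will be positive".
- CRC among positives: 10 %.

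Positives: 33,600 × 0.10 = 3,360. CRCs: 3,360 × 0.10 = 336, which agrees with the article.

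**Assumptions not in the article**
- IBD among positives, i: 2–5 %.
- Any adenoma among positives, a: 15–35 %.
- Share of those adenomas above 1 cm, s: 30–70 %.
- Components do not overlap, every positive patient has a colonoscopy, and every adenoma is coded.

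**Formulas and results**
- As defined, 10 + i + a × s: from 10 + 2 + 15 × 0.3 = 16.5 % to 10 + 5 + 35 × 0.7 = 39.5 %.
- Counting every adenoma, 10 + i + a: from 10 + 2 + 15 = 27 % to 10 + 5 + 35 = 50 %.
- Counting none, 10 + i: from 10 + 2 = 12 % to 10 + 5 = 15 %.

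These ranges overlap because the assumptions vary together. Within any one scenario the errors are:
- Overstatement if all are counted, a × (1 − s): from 15 × 0.3 = 4.5 to 35 × 0.7 = 24.5 percentage points.
- Understatement if none are counted, a × s: from 15 × 0.3 = 4.5 to 35 × 0.7 = 24.5 percentage points.

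Patients with an adenoma code of unresolved size: 3,360 × 0.15 = 504 to 3,360 × 0.35 = 1,176.

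**The case against.** The strongest reply is that this is a condensed article and its source list is not complete. Data collection names no source for urgent referrals either, although these are a listed outcome, so a missing source does not show that none is planned. The personal identification number allows linkage to further registers, and code lists and derivations usually belong in the full protocol or SAP. Identifying findings by codes also does not strictly exclude using other information to size an adenoma.

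Much of this stands as a limit on the claim. A reader might infer that none of the registers holds size, or that the endpoint cannot be computed by any route. The documents do not support either: they do not describe the registers' fields, and they show only that no named source is said to supply size. A reader might also infer that the listed colonoscopy outcome fails. It does not: a tabulation of all ICD-10 codes can be produced as written, and the PPV of serious bowel disease is not in the outcome list.

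The numerical illustration is also open to challenge. Apart from the 10 % for CRC, its inputs are assumed. A patient can have both a cancer and an adenoma, and whether GPs refer positives is itself a study outcome, so full colonoscopy uptake is not given.

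The reply does not remove the conflict. The article is not silent on method. It names codes as the basis in two sections, and that basis does not supply an attribute the definition requires. An SAP that followed the text would inherit the problem, and one that used another source would have to go beyond the published method.

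**Conclusion.** The concern holds for one component of one descriptive summary. By the stated method, the size criterion for adenomas cannot be applied, so the composite PPV cannot be derived as defined. CRC and IBD remain identifiable, and the PPV for CRC and the sample size do not change.

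Provided adenomas are coded when found, the direction of each error follows from the definition: counting all coded adenomas cannot lower the PPV, and counting none cannot raise it. The size is unknown, because the documents give no adenoma or IBD rates. The assumed ranges show only that the choice could matter a good deal; they do not estimate the bias. Overlap between components would reduce the differences. The point should be settled before analysis, but it does not threaten the trial's other results.

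**What to change.** Before analysis, do one of the following and state it in the protocol or SAP:

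1. Name an existing source, linkable by the personal identification number, that records adenoma size for colonoscoped iFOBT-positive patients (endoscopy or pathology reports, for example), and use it to apply the 1 cm criterion. The definition then stands. The cost is one further data extract.
2. If no such source is available, define the register-based composite as CRC or IBD, and report coded adenomas of any size as a separate component with no size claim. This needs only a change of wording. The cost is a narrower composite and a less specific adenoma component.

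The first option is preferable where the data exist, because it keeps the sponsor's own definition of serious bowel disease. Under either option, reporting the PPV by component would show how much of the composite depends on adenomas.

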### Analysis of the iFOBT and determination of clinical cut-off

In the Danish screening programme, the iFOBT is analysed on OC-Sensor DIANA (Eiken Chemical Company, Ltd, Japan). In the CDR, the analysis is performed at the Department of Clinical Biochemistry at the Regional Hospital of Randers. All iFOBTs requested from general practice during the study period will be analysed using this existing infrastructure in parallel with the screening samples. iFOBTs are analysed continuously and done by staff blinded to colonoscopic findings.

Studies of iFOBT cut-off values have primarily been conducted in a screening setting [45–49]. The cut-off value in the Danish screening programme is set to 100 μg/L. To our knowledge, no studies have investigated an optimal cut-off value for patients presenting non-alarm symptoms of CRC. Small amounts of blood loss in faeces are normal, but no exact reference level exists [50]. On the other hand, small amounts of blood in faeces may also be indicative of CRC. A low cut-off value for blood in stools increases the number of false positive test results and consequently the number of performed colonoscopies and required resources, whereas a high cut-off increases false negative test results and thereby introduces a risk of delay in the diagnosis [31, 51]. In this study, we set the cut-off value to 50 μg/L. Thus, a value of <50 μg/L will be considered as negative and ≥50 μg/L as positive.

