### Statistical analysis

The study uses a cluster-randomised stepped-wedge design [40]. Therefore, analysis of data will follow the recommendations for this study design. Each general practice will serve as a control until crossing over to intervention. As iFOBT is not available to Danish GPs before they are included in the study, it will not be possible to compare the use before and after inclusion. However, we will be able to evaluate the dissemination of the test in general practice.

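### For CRC number and stage, the plan sets a historical comparison that contradicts its own stepped-wedge analysis and cannot separate iFOBT from calendar time

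*Protocol article*

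**What the plan says.** The Statistical analysis section of the protocol article opens with a general commitment: "Therefore, analysis of data will follow the recommendations for this study design". It then names the source of control data: "Each general practice will serve as a control until crossing over to intervention". It makes one exception, for use of the test itself: "As iFOBT is not available to Danish GPs before they are included in the study, it will not be possible to compare the use before". That exception does not extend to cancers, stage, colonoscopies or referrals.

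The subsection on clinical implications gives the contrasts outcome by outcome:

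- **Number of CRCs:** "The number of CRCs diagnosed in the study period is compared with the number of CRCs diagnosed before introducing iFOBT in general practice".
- **Stage:** "The same comparison is done for stage distribution of CRC".
- **Colonoscopies and urgent referrals:** "Age- and sex-standardised number and rates of colonoscopies and urgent referrals in the CPP are estimated before and after intervention".
- **Colonoscopy findings and the PPV for serious bowel disease:** no before/after contrast is given.

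On timing, Design and Fig. 1 bring municipalities in over seven monthly dates within a one-year study. The randomised month governs when the CME is offered. Actual inclusion follows the month in which the CME is held, which the GPs may choose, or the month after they decline.

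On concurrent activity, study samples are "analysed using this existing infrastructure in parallel with the screening samples". The Background lists screening among the initiatives meant to shift CRC towards earlier stages.

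**The concern.** In a stepped wedge, exposure rises with calendar time by design. The protection against time trends comes from comparing clusters that have crossed over with clusters that have not, in the same months. The contrast stated for CRC number and stage gives this up: it sets the whole study period against an earlier one. Three things follow.

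1. Months in which a municipality is still a control are counted on the after side.
2. Any change between the two periods in screening, referral or registration is read together with the iFOBT effect. Age and sex standardisation does not remove it.
3. Stage is compared as a distribution, so the stage IV share can fall because the denominator grew.

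These are the outcomes closest to patient benefit, and the Discussion presents the study as controlled and as a basis for future recommendations.

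**Working it through.** **1. The plan's own figures (Sample size).** Expected CRCs found by iFOBT: 33,600 × 0.10 × 0.10 = 336, as stated. The detectable fall in stage IV from 25% to 16% (alpha 0.05, taken as two-sided; power 0.80) reproduces in two ways, and the document does not say which was used:

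- Equal groups: 315 per group, or 337 with continuity correction (close to 336).
- 800 annual CRCs split 200 control and 600 exposed: power 79.6%.

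A comparison of 800 with 800, as in a study year against one earlier year, does not reproduce it: power would be 99.4% and the detectable share 19.2%. Neither matching version includes clustering or period effects.

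**2. Unexposed time inside the study period.** Inputs: a 12-month study and seven start months. Assumption: even spread over the starts. Exposed months are 12, 11, 10, 9, 8, 7 and 6, which sum to 63 of 7 × 12 = 84. Exposed share = 63/84 = 0.75.

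Observed ratio = (0.25 + 0.75 × RR) × (1 + trend). For RR = 1.20 and no trend: 0.25 + 0.90 = 1.15. With 19 municipalities placed 3, 3, 3, 3, 3, 2, 2, the control share is 52/228 = 22.8% and the ratio is 0.228 + 0.772 × 1.20 = 1.15 again.

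**3. Calendar trend.** The documents give no trend, so these drifts are assumptions. With RR = 1 the ratio is 1 + trend: 1.05, 1.10 or 1.20 for a drift of 5%, 10% or 20%. The subsection names no test for these outcomes. If two annual counts were tested at the two-sided 5% level, z = 800d / √(800 + 800(1 + d)):

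| Drift, no iFOBT effect | Chance of a significant result |
|---|---|
| Count +5% | 17% |
| Count +10% | 50% |
| Count +20% | 97% |
| Stage IV 25% to 23% | 15% |
| Stage IV 25% to 21% | 48% |
| Stage IV 25% to 19% | 83% |

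The stage rows use a two-proportion test with 800 per period. With no drift the rate is 5%.

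**4. Stage share.** Sample size gives about 800 CRCs a year and 25% stage IV, so 200 cases. Share = 200/(800 + x), where x is the number of extra early diagnoses:

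- x = 0: 25.0%
- x = 100: 200/900 = 22.2%
- x = 200: 200/1,000 = 20.0%

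Stage IV cases stay at 200 throughout. The values of x are illustrative; the plan does not say how many of its 336 would be additional in the year.

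**5. Cost of a period-adjusted analysis.** Assumptions: 19 equal clusters, starts as in the second layout above, about 800/(19 × 12) = 3.5 CRCs per cluster-month, ICC 0 to 0.05, Hussey-Hughes variance, actual start equal to randomised start. About 182 of 800 CRCs fall in control months. For 25% to 16%:

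| Model | Power, ICC 0 | Power, ICC 0.05 |
|---|---|---|
| No period effects | 75% | 71% |
| Fixed period effects | 48% | 40% |

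With period effects the detectable difference is 13 to 15 percentage points.

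**The case against.** The strongest reply is that the Statistical analysis section already commits to stepped-wedge recommendations, and that model terms are the kind of detail a condensed article leaves to a fuller document. This answers part of the point. A reader might infer that the randomised controls go unused throughout; the general commitment does not support that. A reader might also infer that every clinical-implication outcome is a historical comparison. That too fails: colonoscopies and referrals can be read as before and after each practice's own crossover, and colonoscopy findings and PPV have no such contrast. For colonoscopies and referrals, not naming a period term is not in itself a fault of an article.

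A further tempting inference is that screening biased the comparison. The documents show that screening runs alongside the study. They do not show that it was new or that its coverage changed, and stable screening would produce no trend.

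It is also fair that dilution pulls towards the null and creates no false positives. Reporting the CRC count beside the stage distribution would also let a careful reader see an unchanged stage IV count. The plan itself calls stage IV secondary and possibly underpowered.

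What remains is that CRC number and stage have an explicit contrast that differs from the general commitment. That is a conflicting instruction, not omitted detail, and the only stated exception to the design's comparison concerns test use.

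**Conclusion.** The point holds for number of CRCs and stage distribution. The plan gives two incompatible comparisons for them, and the more specific one is open to any calendar trend and mixes control time into the study period. The dilution is modest (1.20 read as 1.15) and rests on even starts. The trend bias equals whatever the trend is; its size and direction are not known from the documents, and it could hide an effect as well as mimic one. The stage-share artefact is arithmetic, but its size depends on how many extra early cases are found.

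Colonoscopies and urgent referrals are touched only in that a before/after-crossover contrast also needs calendar-period adjustment. Colonoscopy findings, PPV, and the aims on uptake and diagnostic value are not affected.

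**What to change.** Reconcile the general Statistical analysis statement with the clinical-implications subsection by replacing the historical comparison:

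- **Contrast:** exposed against not-yet-exposed cluster-months within the wedge, on the register data already listed under Data collection.
- **Model:** fixed calendar-period effects, cluster effects and a small-sample correction. State whether there are 19 clusters (municipalities) or 18 (GP units, since Samsø belongs to the Aarhus unit). Use the same period adjustment for colonoscopies and urgent referrals.
- **Exposure:** analyse by randomised start month first and by actual start second, because Design lets actual inclusion follow the CME month the GPs choose.
- **Stage:** report stage IV as a rate per listed person-time beside the share.
- **Screening:** separate screen-detected cases only as a sensitivity analysis, if the registers allow it. Data collection lists no detection-mode variable.

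A before/after description can stay if it is labelled descriptive.

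The cost is revised wording and more modelling, with no new data source for the main analysis. Intervals will be wider, and under the assumptions above power for 25% to 16% falls to about 40–48%. Sample size partly concedes this already. Analysis by randomised month will also dilute the effect where actual starts differ.

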**Fig. 1 Fig1:**
[figure not shown]
Stepped-wedge design used for the study. Most municipalities start out as usual care (C). Within the first seven months, all will cross over to intervention (I). Seven possible dates of inclusion are available; the 19 municipalities are randomly distributed between these

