We found it important to develop a clinical instruction to direct the use of iFOBT in patients presenting with non-alarm symptoms of CRC. We acknowledge that the clinical assessment performed by the GP should guide the exact use. Therefore, the indications presented in the instruction are suggestions. This implies that GPs can request iFOBT for other symptoms or signs that they may find relevant. This gives us the opportunity to explore if the GPs’ needs for the test are in line with the indications in the clinical instruction. The criteria for urgent referral in a CPP are evidently not definite, eg change in bowel habits can be of different levels of severity and could be a symptom of many different diseases. Furthermore, the threshold for referring patients on the basis of a given alarm symptom might be lower for some GPs than for others. Consequently, we decided to include anaemia, change in bowel habits and abdominal pain in the clinical instruction. This is supported by a recent update of the guideline provided by the National Institute for Health and Care Excellence (NICE) [58]. However, it is important to underline that performance of the iFOBT in this study only consider individuals who are not eligible for urgent referral in the CPP for CRC. Giving GPs the possibility of performing iFOBT on ‘low-risk-but-not-no-risk’ patients may result in more complete and timely diagnostic workup.

Using a cluster-randomised stepped-wedge study design allows inclusion of all GPs in the CDR. Using municipalities as clusters implies that all GPs in a given municipality are included at the same time. Thereby, we prevent that some GPs in the municipality are able to order the test, while others are not. Furthermore, this setup provides the opportunity of arranging the CME at a meeting for all GPs in the municipality. This allows GPs to meet and discuss the study with colleagues from their own clinical environment.

Using iFOBT in patients who present non-alarm symptoms of CRC may imply faster and earlier diagnosis. This study constitutes a thorough large-scale investigation of iFOBT in a real-life setting in general practice. The study design enables generalisability to other primary-care settings and will nationally and internationally be very important in deciding future recommendations for diagnostic workup of patients presenting symptoms of CRC.

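### The one-year before/after comparison of CRC numbers cannot separate diagnoses brought forward by iFOBT from additional ones, and the stage IV share can be diluted through the same denominator

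*Protocol article*

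**What the plan says.** The statistical analysis section on clinical implications states: "The number of CRCs diagnosed in the study period is compared with the number of CRCs diagnosed before introducing iFOBT in general practice". The next sentence applies the same comparison to stage distribution. The Outcomes section lists the CRC number as standardised for age and sex; the analysis section does not repeat this, but the two are compatible.

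The Sample size section says that "the study is rolled out sequentially and the study period is 1 year", and no later count of CRCs is described. Fig. 1 and the Design section have all municipalities crossing over within the first seven months, so the study year also contains control time before inclusion.

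On the expected effect, the Discussion says: "Using iFOBT in patients who present non-alarm symptoms of CRC may imply faster and earlier diagnosis". On the expected yield, the Sample size section says: "we expect to find approx. 336 CRCs by the use of iFOBT during the study period", against about 800 CRCs a year in the region. The Statistical analysis section also says, in general terms, that the analysis will follow the recommendations for stepped-wedge designs.

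**The concern.** If the test works as the Discussion hopes, some cancers that usual care would have diagnosed after the study year are diagnosed within it. In each municipality the number rises after inclusion for about as long as the lead time and then returns to its former level, even if no cancer is found that would otherwise have stayed undiagnosed. One contrast over one year, with nothing observed afterwards, gives the same result for this temporary shift as for a real gain in yield. Standardising for age and sex does not change that.

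The stage comparison shares the problem. Advanced cases that are not stage IV enlarge the denominator, so the stage IV share can fall while the number of stage IV cases is unchanged.

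The study year also mixes months before and after inclusion, so the contrast is not a clean comparison of exposed with unexposed time.

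At stake is how a rise in CRCs, or a fall in the stage IV share, can be interpreted when the results are used to plan CRC diagnostics.

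**Working it through.** **Reproducing the plan's figure.** The Sample size section gives "we expect that 33,600 iFOBTs will be performed during the study period", "we estimate that approx. 10 % of performed tests will be positive" and "we estimate that 10 % of the patients with a positive test will be diagnosed with CRC". So 33,600 × 0.10 × 0.10 = 336, as stated.

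**Exposure.** Assume seven equal monthly steps starting in month 1. Municipalities then have 12, 11, 10, 9, 8, 7 or 6 exposed months, a mean of 9.0. The control time inside the study year is therefore already allowed for. Test-found CRCs per region-month of exposure: 336 / 9 = 37.3. Usual number per month: 800 / 12 = 66.7.

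**Upper bound: all 336 advanced, none added.** The lead time L is an assumption, shown as a range. Excess = 336 × L / 9. The z value comes from a Poisson comparison of the study year with a prior year of 800: z = excess / √(1600 + excess).

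| L (months) | Excess | % of 800 | z |
|---|---|---|---|
| 1 | 37 | 4.7 | 0.92 |
| 2 | 75 | 9.3 | 1.82 |
| 3 | 112 | 14 | 2.71 |
| 6 | 224 | 28 | 5.24 |

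**Is this bound compatible with the article's other figures?** If none of the 336 is additional, the test accounts for 37.3 / 66.7 = 56 % of all CRCs in exposed time. The Background says that 50 % of CRCs present with vague or non-specific symptoms and gives a sensitivity of 80–90 % (from screening studies). Even with every such patient tested, the test can account for at most 66.7 × 0.5 × 0.8 = 26.7 to 66.7 × 0.5 × 0.9 = 30 CRCs per exposed region-month.

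| L (months) | All such patients tested: excess (z) | Half tested: excess (z) |
|---|---|---|
| 1 | 27–30 (0.66–0.74) | 13–15 (below 0.4) |
| 2 | 53–60 (1.31–1.47) | 27–30 (0.66–0.74) |
| 3 | 80–90 (1.95–2.19) | 40–45 (0.99–1.11) |
| 6 | 160–180 (3.81–4.27) | 80–90 (1.95–2.19) |

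**Stage IV share.** The article's 25 % of 800 is 200 cases. If these stay at 200 and all advanced cases are stage I–III (assumption), the share becomes:
- 200 / 880 = 22.7 % to 200 / 890 = 22.5 % with an excess of 80–90;
- 200 / 912 = 21.9 % with 112;
- 200 / 1024 = 19.5 % with 224.

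**Would a stepped-wedge model alone solve it?** Take 19 municipalities, seven steps, 12 months, calendar-month terms and an exchangeable correlation. Let the true excess last three months after inclusion and then vanish. Its mean over exposed months is 0.32 of its peak. A single constant on/off effect would estimate it as 0.87, 1.00 and 1.13 of the peak at ICC 0.01, 0.1 and 0.5. Separate effects for months 1–3, 4–6, 7–9 and 10–12 after inclusion recover 1, 0, 0, 0. The protocol specifies no on/off model; the calculation shows only why effects by time since inclusion are needed.

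**The case against.** A reader might infer that the trial will count brought-forward cancers as extra cancers found, or will report significantly more CRCs. The document does not support this. It says only that numbers are compared. It names no test and no decision rule for this outcome, and it lists no measure such as colonoscopies per additional cancer. Earlier diagnosis is the stated hope, so a temporary rise would be the intended effect becoming visible, and stage is examined alongside. It would also be wrong to call the outcome a crude count, since the Outcomes section standardises it, or to charge the trial with a roughly three-fold overstatement from an on/off model that it never states.

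The size is uncertain too. The lead time is not in the documents. The case where all 336 are advanced conflicts with the article's 50 % and 80–90 % figures, and short lead times or partial uptake leave the excess within chance.

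These objections limit the claim but do not remove it. The contrast and the one-year period are stated, not left open, and they cannot distinguish the expected mechanism from added yield. Stage distribution does not settle the matter, because the share depends on the same denominator. Details of the stepped-wedge model may stand in an analysis plan that is not shown, but the before/after number is what this document fixes.

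**Conclusion.** The concern holds in a limited form. The standardised one-year comparison mixes earlier with additional diagnoses, it includes control time before inclusion, and the stage IV share can be diluted through the same denominator.

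Under an assumed 3-month lead with no added cancers, the spurious excess is at most about 80–90 on 800 (z about 2.0 to 2.2) if all patients with non-alarm presentation are tested, and about 40–45 (z about 1.0 to 1.1) if half are. The figure of 112 is an upper bound that the article's other figures do not support. At 1–2 months the excess is within chance; at 6 months it would not be if uptake were near complete.

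These sizes rest on seven equal steps, a constant lead time, Poisson variation and a sensitivity carried over from screening. The plan should be changed on this point, but the document contains no false conclusion to correct.

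**What to change.** In the analysis section on clinical implications:

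1. Replace the before/after number by the CRC rate per listed person-time, adjusted for age and sex. Compare exposed with unexposed time under the randomised roll-out, with calendar-month terms and separate effects by time since inclusion, for example 1–3, 4–6, 7–9 and 10–12 months.
2. Report stage IV also as a rate per person-time, not only as a share of CRCs.
3. State in advance that an early or one-year excess will be reported as compatible with earlier diagnosis and not as additional cancers.
4. Optionally, extend the register extract by 12 months after the study year, as supportive evidence only. No unexposed municipality remains after month 7, so calendar trend is then uncontrolled and persistence of the excess cannot be judged against concurrent controls.

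No new patients are needed, and the CRC data already come from a register. The cost is precision in the later bands. At ICC 0.1, in the layout used above, the standard errors are about 0.23, 0.33, 0.43 and 0.54 of the cluster-period SD for the four bands, against 0.23 for a single effect. If the extract is extended, the final CRC result also comes later.
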